### Trial assessments

Children enrolled in the trial are followed up for up to 120 h post-enrolment or until the first primary endpoint is reached which means diarrhea resolution, whichever is earlier. The schedule of enrolment, intervention, and outcome assessments is shown in Table 2, which follows the SPIRIT (statement provides evidence-based recommendations for the minimum content of a clinical trial protocol) guidelines Table 4.

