#### Definitions

Duration of diarrhea in hospital: time in hours, from randomization till resolution of diarrhea.Resolution of diarrhea: the passage of the last liquid or semi-liquid stool before one soft/formed stool or no stool for 12 h [18].Stool output: The weight of stool in g/kg of admission body weight expressed per time period (i.e., per 24 h and for the entire duration of diarrhea).ORS and plain water intakes: The total volume (in ml) of ORS or plain water is taken per kg of admission body weight, expressed per time period.Treatment failure: If diarrhea continues for more than 120 h after enrollment, or requires unscheduled IV fluids due to progressive dehydration, requiring transfer to the general in-patient wardUn-scheduled IV: When intravenous rehydration fluids are given due to the inability of the ORS to maintain hydrationNon-compliance: inability to consume ≥ 80% of ORS

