### Statistical considerations

#### Sample size and power

The total sample size is 312 male children. In previous non-cholera studies of children comparing an anti-diarrheal to placebo [19–22], the effect sizes for the hourly duration of diarrhea and 24-h stool volume ranged from 0.3 to 1.0 (duration) and 0.3 to 0.7 (stool output), respectively. Outcome improvements ranged from 15 to 45% with treatment (vs. placebo). A clinically significant improvement of 20% produces effect sizes of 0.4 to 0.7 (duration) and 0.3 (stool output) using the pooled standard deviations reported within each outcome. When applied to conventional alpha (0.05) and beta (0.20) values, between 32 and 174 patients per group are required for statistical significance. The maximum anticipated accrual rate of 3 patients per week over 24 months results in 156 patients per group, or 132 patients per group assuming 15% attrition. Therefore, the final anticipated patient group numbers are estimated to provide >99% and 68% power to detect a 20% difference in hourly diarrhea duration and 24-h stool output, respectively.

Justification for the content of the excerpt, based on an independent samples *t*-test (in the Data Analysis part), is reviewed in Table 3. Our sample size estimates were based on detecting a difference in the primary outcome variable (duration of diarrhea). We acknowledge that we were underpowered for secondary outcomes such as stool volume. The secondary outcomes in our study were better classified as exploratory outcomes, which is why we are not adjusting our alpha for multiple endpoints.

**Table 3 Tab3:** Duration of diarrhea (days^a,b^)

Study	M_t_	SD_t_	M_p_	SD_p_	Mdiff	%diff	SDpooled	ES	20%_diff_	ES	nreq	nact	%op
Cojocaru^a^	4.05	1.48	5.73	1.77	1.68	29.3	1.62	1.0	1.14	.71	32	132	99
Santos^b^	4	2.1	4.7	2.2	0.7	14.9	2.15	0.3	0.94	0.44	81	132	99

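### Table 3 plans on uncapped durations while the endpoint stops at 120 h: a true 20% reduction would be recorded as about 13–16 h (11–17%), and the second row's 99% power should be 94%

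*Protocol article*

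**What the plan says.** Under Definitions, the endpoint is "Duration of diarrhea in hospital: time in hours, from randomization till resolution of diarrhea". Under Trial assessments, observation is limited: "Children enrolled in the trial are followed up for up to 120 h post-enrolment", or until resolution if that comes first. A child still unresolved then is classed as a treatment failure ("If diarrhea continues for more than 120 h after enrollment") and transferred. The article gives no duration value for such a child in the comparison of durations.

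Sample size and power sets the target: "A clinically significant improvement of 20% produces effect sizes of 0.4 to 0.7 (duration) and 0.3 (stool output"). Table 3 derives the duration figures from two cited placebo comparisons, in days. The first row reads "4.05 1.48 5.73 1.77 1.68 29.3 1.62 1.0 1.14 .71 32 132 99" and the second "4 2.1 4.7 2.2 0.7 14.9 2.15 0.3 0.94 0.44 81 132 99". In order, the entries are treated mean and SD, placebo mean and SD, difference, percentage difference, pooled SD, effect size, 20% difference, its effect size, required n, planned n and power. The text claims more than 99% power for duration with 132 per group, based on a t-test.

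Nothing in that section refers to the 120 h limit. Nor does it say whether the cited durations run from onset or from start of treatment, although the inclusion criteria admit children with up to 48 h of prior diarrhea. Statistical analysis plans a t-test or Mann-Whitney test of duration, with life-table, log-rank and Cox analyses in addition. It also plans a blinded interim look at pooled duration to see whether the sample size assumptions are correct.

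**The concern.** The planning difference and the endpoint are on different scales. A mean taken over durations that may exceed five days is not the mean of durations observed only to five days. If many control children are unresolved at 120 h, a treatment that truly shortens diarrhea by 20% will show a smaller difference in recorded means.

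Two things depend on this. The protocol calls 20% clinically significant, so a product that meets that target could be reported with a visibly smaller percentage. And if the blinded interim check takes Table 3 as its benchmark, it compares capped durations from randomization with uncapped durations of unstated origin.

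**Working it through.** **Inputs.** From Table 3: placebo mean m = 5.73 d with pooled SD s = 1.62 d (first row); m = 4.7 d with s = 2.15 d (second row). From Sample size and power: alpha 0.05, beta 0.20, 132 per group after attrition. From Trial assessments: window c = 120 h = 5 d. Sidedness is not stated, but the required n fits only a two-sided test.

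**1. Reproduce the plan.** Effect size d = 0.2m/s; required n = 2(1.96 + 0.84)²/d² ≈ 15.7/d²; power = Φ(d√(132/2) − 1.96).

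- First row: 0.2 × 5.73 = 1.146 d = 27.5 h; d = 1.146/1.62 = 0.71. Required n = 15.7/0.71² = 31.1 (printed 32). Power = Φ(0.707 × 8.124 − 1.96) = Φ(3.79), above 99.9%. This agrees with the table.
- Second row: 0.2 × 4.7 = 0.94 d = 22.6 h; d = 0.94/2.15 = 0.437. Required n = 15.7/0.44² = 81.1 (printed 81). Power = Φ(0.437 × 8.124 − 1.96) = Φ(1.59) = 94.4% (noncentral t 94.3%). The printed 99% does not reproduce. With 156 per group it is 97%. A one-sided test at 132 also gives 97%, and would need 65 per group, not 81.

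**2. Compare with the window.** 5.73 × 24 = 137.5 h, which is 17.5 h beyond 120 h. 4.7 × 24 = 112.8 h, which is 7.2 h inside it.

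**3. Apply the cap.** Assumptions: durations run from randomization, unresolved children are scored at 120 h, and the treated mean is 20% lower with the same SD. For a normal shape, E[min(T, c)] = mΦ(z) − sφ(z) + c(1 − Φ(z)), with z = (c − m)/s.

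- First row, control: z = −0.45, 67% unresolved, mean 111.7 h. Treated (m = 4.584 d): z = 0.26, 40% unresolved, mean 99.0 h. Difference 12.7 h, or 11%.
- Second row, control: z = 0.14, 44% unresolved, mean 95.6 h. Treated (m = 3.76 d): z = 0.58, 28% unresolved, mean 81.2 h. Difference 14.4 h; with negative values set to zero, 13.8 h, or 14%.

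The shape is not given, so three were simulated at 132 per group:

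| Row, shape | Unresolved, control/treated | Recorded difference | Effect size | t-test power |
|---|---|---|---|---|
| First, normal | 67% / 40% | 12.7 h (11%) | 0.58 | 99.7% |
| First, lognormal | 64% / 34% | 14.0 h (12%) | 0.79 | >99.9% |
| First, gamma | 65% / 36% | 13.7 h (12%) | 0.72 | >99.9% |
| Second, normal | 44% / 28% | 13.8 h (14%) | 0.40 | 90% |
| Second, lognormal | 36% / 21% | 16.0 h (17%) | 0.58 | 99.7% |
| Second, gamma | 39% / 24% | 15.7 h (16%) | 0.52 | 99% |

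Log-rank power is about 99.9% or more (first row) and 89–96% (second row).

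**4. If the durations run from onset.** Shift the means down by 1 or 2 days, keep the SDs and cap at 120 h. The answer depends on what 20% means:

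- Kept as the absolute 1.146 or 0.94 d: power about 92% or more in every case.
- Applied only to the remaining duration: first row 95% or more. Second row, across shapes, 76–97% with 1 day elapsed and 50–83% with 2 days.

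**5. The interim benchmark.** Uncapped, the first row's pooled mean under the planned effect is (137.5 + 110.0)/2 = 123.8 h, which a 120 h window cannot record. Capped (normal), it is (111.7 + 99.0)/2 = 105.4 h. For the second row the two figures are (112.8 + 90.2)/2 = 101.5 h and (95.8 + 82.1)/2 = 89.0 h. With the assumptions exactly right, the blinded mean would sit 12 to 18 h below an uncapped benchmark.

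**The case against.** The strongest reply is that the trial still works. Power stays above the 80% criterion because the cap shrinks the SD along with the difference. The planned log-rank and Cox analyses treat 120 h as ordinary censoring. The 20% is a sample-size input; no section makes it a pass mark for the result, and the interim paragraph names no benchmark. The time origin of the cited durations lies in studies not shown here. All of this stands, and it limits the point to the stated planning figures and their interpretation. It does not make those figures describe the recorded endpoint.

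A reader might infer more than the document supports:

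- That the window is at or below both planning means. It exceeds 4.7 days by 7.2 h.
- That the planned effect cannot appear. About 13–16 h remains in the mean, and the second row's difference in medians stays at about 22–24 h.
- That the effect size necessarily falls. The capped values, 0.58–0.79 and 0.40–0.58, straddle the printed 0.71 and 0.44.
- That the trial is underpowered. A figure near 50% requires subtracting a full 48 h, the eligibility maximum, from every child, applying 20% only to the remainder, and assuming a normal shape.
- That the planned effect fails on either time origin. From onset, an absolute difference of 0.94–1.146 d could carry over to the period after randomization.

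**Conclusion.** The mismatch is in the article itself: the planning durations are uncapped and the endpoint ends at 120 h. If the durations run from randomization and unresolved children are scored at 120 h, roughly two thirds (first row) or 36–44% (second row) of controls reach the cap, and a true 20% reduction in the mean is recorded as 11–17%. Both conditions are assumptions, and the range reflects the unknown shape.

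Detectability is not the issue on that reading, since power remains about 90% or more. On the onset reading, power ranges from about 50% to nearly 100% according to how the 20% is defined, so the article should say which is meant.

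One figure is wrong irrespective of time origin or cap: on its own inputs, the second row's power at 132 per group is 94%, not 99%. The text's claim of more than 99% holds only for the first row. With the cap, the second row gives 90% to over 99%, depending on shape.

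**What to change.** In Sample size and power and Table 3:

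- Restate the control mean and SD, the expected proportion unresolved at 120 h, the 20% difference, the effect size and the power for hours from randomization within the 120 h window. State the distribution and the scoring of unresolved children used in that calculation.
- State whether the planning durations are taken to run from onset or from start of treatment. If from onset, state whether the 20% is an absolute difference or a fraction of the remaining duration.
- Correct the second row's power, and give the power claim in the text as a range across the two rows.
- Name the restated values, pooled over both arms, as the benchmark for the blinded interim check.

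This is a re-expression of planning figures. Follow-up and enrolment need not change. The cost is that some stated figures become less favourable, chiefly the second row's power and the difference in hours expected on the recorded endpoint.

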#### Treatment procedures

The study patients are placed on diarrhea cots. Initial treatment dosing with WHO-ORS or VS002A is estimated using bodyweight following 5–10 ml/kg after each loose stool as per icddr,b guideline, to maintain the ongoing loss. Adjustments may be required and hydration is maintained using smaller or larger volumes depending on measured losses. Children are fed using a spoon. Assessment and treatment are to continue until the resolution of diarrhea. The child is supplemented with tablet zinc: one tablet (20 mg) per day for 10–14 days [2].

In young children who cannot control micturation, a pediatric urine collection (PUC) bag is applied to facilitate the separate collection of stool and urine.

The patient receives liquid, semi-solid, and solid foods appropriate for age. Breast-fed children continue to receive breast milk. If stool culture reveals any pathogen, then the patients receive an appropriate antibiotic if applicable and are excluded from the study (e.g., azithromycin in cholera). Intakes of ORS, food, and medicines are supervised by a nurse and are recorded. Vital signs are recorded for each patient every 4 h. Intake of ORS and water is recorded every 4 h while outputs of stool and urine and vomitus, and stool frequency are recorded continuously. Clinical assessment of the study children is performed by the study investigators and/or designated research physicians. Vital signs and body weight are measured and recorded by experienced nurses of the Study Ward. And other measurements, e.g., stool frequency and volume/weight, intake of rehydration fluids, and urine outputs are measured by designated health workers under the supervision of the study nurse who would record them. Each participating child is closely monitored for the occurrence of any adverse events such as worsening diarrhea or increased vomiting, and their severity and duration are noted and information is also recorded for analysis.

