### Discontinuation procedure

#### Criteria for removal from study and treatment failure

Patients are discharged from the hospital when diarrhea is resolved (the working definition of resolution of diarrhea has been mentioned below). However, no participants are discharged before 24 h from enrolment.If it takes more than 5 days (≥ 120 h) to resolve diarrhea or if a patient becomes dehydrated requiring unscheduled IV fluids, we transfer the patient to the general in- patient’s ward for further evaluation and treatment. In that case, it is considered a “treatment failure.”After enrollment, if any patient develops any co-morbidity like pneumonia, sepsis, electrolyte imbalance or requires specific antibiotics and/or special attention/intervention, we transfer the patients to the General ward or ICU of the hospital and are removed from the study. The reason for removal is recorded and an off-study document is completed by the study team.Patients who decide to withdraw from the study are defined as “drop-out.”Patients who do not consume at least 80% of ORS offered are considered “non-compliant”.If stool culture reveals an agent that needs antibiotic therapy, the patient is removed from the study, and an off-study document is completed by the study team.All data collected on randomized subjects are kept for intent-to-treat analysis, including patients who withdrew from the study (drop out), have co-morbidity, or are defined as treatment failures or non-compliant.

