#### Recording of adverse events

All adverse events regardless of the seriousness, severity, or relationship to the study medication are recorded on the adverse events pages of case record forms. Adverse events that meet the definition of a serious adverse event are to be reported on the serious adverse event form provided for this study. Adverse events will be documented in clear, unambiguous medical language. All adverse events not resolved by the end of the study or that have not been resolved upon the subject’s discontinuation in the study will be followed until the event resolves, the event stabilizes, or the event returns to baseline if a baseline value is available. All serious adverse events are to be reported to the secretariat of the Ethics Review Committee of icddr,b within 24h of the investigator or their staff becoming aware of them. Reporting is performed by recording as much information as is available at the time on the serious adverse event (SAE) form by icddr,b IRB.

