#### Statistical analysis

Data are collected on paper and entered electronically capturing information such as demographics, medical history, clinical assessments, clinical course, etc., and transcribed into an electronic database using Statistical Package for Social Sciences (SPSS) (version 20), STATA, or equivalent. The primary analysis will be intended to treat analysis which will include all of the patients who were randomized in the study. A per-protocol analysis will also be done only including only those randomized subjects with efficacy data on diarrhea volume and who have taken at least 80% of the investigational product. If the distribution of the variable does not have a normal distribution, a log transformation of data will be performed before the t-test analysis or a non-parametric equivalent test will be performed. Differences between the two treatment groups (VS002A versus WHO ORS) will be examined for baseline characteristics before performing a statistical analysis of the efficacy endpoints. If any differences are considered to be clinically important, subgroup analysis will be presented for the relevant endpoints. Depending upon the normality of distribution of the quantitative variables, a *t*-test or Mann-Whitney *U* test will be used to compare the duration of diarrhea, stool output, the output of vomit, and ORS intake. The chi-squared test will be used to compare treatment failures, unscheduled IV, and frequency of vomiting. Comparison of the primary outcome will be performed with and without adjustment of design effects (age stratum) and patient characteristics (cause, clinical characteristics on admission, nutritional status). All analyses will be performed separately on children as per protocol and on all children on an intention-to-treat basis. In addition, a life-table analysis will also be performed. Time to cessation of diarrhea will be compared by log-rank test, and adjustments of covariates will be made via Cox proportional hazards regression.

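### Vomiting is compared over a stay that ends when diarrhea resolves; a first-24-h version would separate tolerability from duration (minor)

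*Protocol article*

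**What the plan says.** **When observation ends.** The Trial assessments section states: "Children enrolled in the trial are followed up for up to 120 h post-enrolment or until the first primary endpoint is reached". The endpoint meant is resolution, and the earlier of the two times applies. Treatment procedures agrees: "Assessment and treatment are to continue until the resolution of diarrhea". So do the removal criteria: "Patients are discharged from the hospital when diarrhea is resolved", with a lower bound, "no participants are discharged before 24 h from enrolment". Under Definitions, the primary outcome is the time in hours from randomization to that same resolution. Resolution is dated to the last loose stool before a soft or formed stool or 12 h without stool, so a child may be watched for up to about 12 h beyond it.

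**What is counted.** Children are "closely monitored for the occurrence of any adverse events such as worsening diarrhea or increased vomiting". Vomitus is recorded continuously. The Exploratory outcomes list gives stool output, urine output and ORS intake both for the first 24 h and in total. Output and frequency of vomiting are listed with no period.

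**What is compared.** Under Statistical analysis, vomit output goes to a t-test or Mann-Whitney test, and for frequency: "The chi-squared test will be used to compare treatment failures, unscheduled IV, and frequency of vomiting". Neither names a time at risk.

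**After the end.** Under Recording of adverse events, the sentence on open events begins "All adverse events not resolved by the end of the study or that have not been resolved upon the subject’s discontinuation in the study will" and goes on to require follow-up to resolution, stabilization or a return to baseline. That covers events already open. Post-trial care describes advice to return and no data collection.

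**The concern.** The event that closes the observation period is the primary outcome. If VS002A shortens diarrhea, its children are observed for fewer hours and have less time in which to vomit on record. A whole-stay total, or the proportion of children who ever vomit, then favours the faster arm even when hourly vomiting is identical. If VS002A lengthens diarrhea, the effect reverses. If it is somewhat worse tolerated but also faster, part of the excess is hidden.

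Vomiting bears directly on whether children tolerate a new oral solution, and the title promises a comparison of safety as well as efficacy. A reader shown less vomiting with VS002A could not tell better tolerability from shorter illness.

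**Working it through.** **Plan figures used.** The article gives no figure for hours of observation, so there is none to reproduce. Its planned effect is a 20% improvement, and Table 3 turns this into days: 0.20 × 4.7 = 0.94 (stated 0.94) and 0.20 × 5.73 = 1.146 (stated 1.14).

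**Inputs.** Control duration from Table 3, in hours:
- First row: mean 5.73 × 24 = 137.5, SD 1.77 × 24 = 42.5.
- Second row: mean 4.7 × 24 = 112.8, SD 2.2 × 24 = 52.8.

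**Model.** Control duration D is lognormal with σ² = ln(1 + (SD/mean)²) and μ = ln(mean) − σ²/2. Treated duration is 0.8 × D. The observed window is W = min(max(D, 24), 120). A second version uses D + 12, to allow for the stool-free confirmation period. Each setting used 2,000,000 simulated durations.

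**Constant hourly rate, equal in both arms.** Expected events are proportional to mean W.

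| Table 3 row | Extra observation | Control window | Treated window | Shorter by |
|---|---|---|---|---|
| First | none | 111.8 h | 100.6 h | 10.0% |
| First | 12 h | 115.6 h | 107.9 h | 6.7% |
| Second | none | 95.7 h | 83.0 h | 13.3% |
| Second | 12 h | 102.9 h | 92.3 h | 10.3% |

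The range is about 7–13%. Normal instead of lognormal durations give about 6–11%. The loss stays below 20% mainly because of the 120 h cap: 62% of control durations in the first row and 36% in the second reach it.

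**Vomiting clustered early.** Let the rate decay exponentially with mean k = 24, 48 or 72 h. The share of events seen by time W is 1 − exp(−W/k). Without the extra 12 h, the treated arm shows 1.0%, 3.6% and 5.2% fewer events (first row) and 2.4%, 5.9% and 7.9% fewer (second row). This is about 1–8%, and less if the 12 h are added.

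**Effect on the chi-squared test.** Assume 30% of controls vomit at least once, at a constant rate. This run used the pooled SDs of Table 3, which move the windows by about 1 h. The treated arm then shows 27.4% or 26.5% (28.3% or 27.3% with the 12 h). With 156 per arm, a false significant difference arises in about 7% or 10% of trials (5% or 8%).

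**Candidate remedies.** Over a fixed first 24 h both arms have the same window, so the expected ratio is 1.00 whatever time pattern they share. Events per hour observed also give 1.00 if the rate is constant. If vomiting clusters early, dividing by hours overcorrects: 0.976 / 0.867 = 1.13 (second row, k = 24 h) and 0.948 / 0.900 = 1.05 (first row, k = 72 h). The faster arm would then look 5–13% worse.

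**The case against.** **A plan not shown could settle this.** Whether an exploratory outcome is reported as a total, a 24 h value or a rate is often left to the analysis plan, and the schedule in Table 2 is not visible. Because vomitus is charted continuously, either analysis remains possible. This lowers the severity. What remains is that the article itself fixes the end of observation, names the tests, and gives first-24-h versions to the neighbouring outcomes but not to vomiting.

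**Total vomiting is a legitimate measure.** A child who recovers sooner and vomits less overall has gained something real, and the window coincides with the treatment period. This stands. The whole-stay total should be kept and read as burden, not as tolerability.

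**Stronger readings a reader might infer, and why they fail:**
- *That the safety comparison as a whole is biased toward the faster arm.* The stated electrolyte objective rests on blood chemistry read at 24 h in both arms. No between-arm test of adverse events is stated. The point reaches adverse events only if someone tabulates them over the whole stay.
- *That harms are lost in the sickest children.* Transfer for unscheduled IV fluids is counted as treatment failure. Removal from the study is stated for co-morbidity and for culture results needing antibiotics, with the reason recorded. Data already collected are kept for the intention-to-treat analysis, and open adverse events are followed.
- *That the loss approaches 20%.* Assumed in-hospital means of 72 h (SD 36) or 48 h (SD 30) give windows 18% or 17% shorter, or about 15% with the 12 h. Those durations are not in the document.

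**Conclusion.** The point holds in a limited form and is minor. Observation of vomiting ends at the primary endpoint, within bounds of 24 h and 120 h, and the stated comparisons do not allow for this. With diarrhea 20% shorter and equal vomiting rates, the faster arm is observed for about 7–13% less time on the Table 3 figures; early clustering reduces the shortfall in events to about 1–8%.

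The size rests on Table 3 durations applying to time after randomization, a lognormal shape and a uniform 20% shortening. The direction needs only equal vomiting rates over time and different durations. False significance is barely above the nominal level, so the harm lies in interpreting an exploratory tolerability result. The primary analysis and the 24 h blood chemistry are untouched.

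**What to change.** 1. In Exploratory outcomes and Statistical analysis, add vomit output and vomiting frequency in the first 24 h from randomization, and name these as the tolerability comparison. This matches what stool, urine and ORS intake already have. Counting from randomization matters because all children receive WHO-ORS for rehydration before it.
2. Keep whole-stay vomiting as a measure of burden, and report hours observed by arm beside it. A per-hour rate may be given as secondary only, because it overcorrects when vomiting clusters early.
3. Tabulate any between-arm adverse-event summary over the same first 24 h. For children transferred or removed before 24 h, include events found in the hospital record up to that time.

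**Cost.** A few sentences. Vomitus is already charted continuously, and the existing minimum stay covers the first 24 h for every child not transferred, removed or withdrawn. The only added work is the record check for early leavers. Later vomiting falls outside the 24 h comparison but remains in the whole-stay total.
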